## Abstract

**Background:**

Systemic inflammation is associated with various complications in chronic obstructive pulmonary disease including weight loss, cachexia, osteoporosis, cancer and cardiovascular diseases. Inhaled corticosteroids attenuate airway inflammation, reduce exacerbations, and improve mortality in chronic obstructive pulmonary disease. Whether inhaled corticosteroids by themselves or in combination with a long-acting β_2_-adrenoceptor agonist repress systemic inflammation in chronic obstructive pulmonary disease is unknown. The Advair Biomarkers in COPD (ABC) study will determine whether the effects of inhaled corticosteroids alone or in combination with a long-acting β_2_-adrenoceptor agonist reduce systemic inflammation and improve health status in patients with chronic obstructive pulmonary disease.

**Methods/Design:**

After a 4-week run-in phase during which patients with stable chronic obstructive pulmonary disease will receive inhaled fluticasone (500 micrograms twice daily), followed by a 4-week withdrawal phase during which all inhaled corticosteroids and long acting β_2_-adrenoceptor agonists will be discontinued, patients will be randomized to receive fluticasone (500 micrograms twice daily), fluticasone/salmeterol combination (500/50 micrograms twice daily), or placebo for four weeks. The study will recruit 250 patients across 11 centers in western Canada. Patients must be 40 years of age or older with at least 10 pack-year smoking history and have chronic obstructive pulmonary disease defined as forced expiratory volume in one second to vital capacity ratio of 0.70 or less and forced expiratory volume in one second that is 80% of predicted or less. Patients will be excluded if they have any known chronic systemic infections, inflammatory conditions, history of previous solid organ transplantation, myocardial infarction, or cerebrovascular accident within the past 3 months prior to study enrolment. The primary end-point is serum C-reactive protein level. Secondary end-points include circulating inflammatory cytokines such as interleukin-6 and interleukin-8 as well as health-related quality of life and lung function.

**Discussion:**

If inhaled corticosteroids by themselves or in combination with a long-acting β_2_-adrenoceptor agonist could repress systemic inflammation, they might greatly improve clinical prognosis by reducing various complications in chronic obstructive pulmonary disease.

## Background

Chronic obstructive pulmonary disease (COPD) represents an increasing burden worldwide and is reported to be the sixth leading cause of death in 1990 [1] and the fourth in 2000 [2]. Discouragingly, by the year 2020, its mortality rate will rank third, only behind stroke and heart disease [1]. Although these figures are alarming, they are likely to be gross underestimates of the true health and economic burdens of COPD because COPD is an important risk factor for other causes of morbidity and mortality, including cardiovascular disorders and cancer [3,4].

While the pathobiology of COPD has not been fully elucidated, there is a growing recognition that systemic inflammation may play a salient role in COPD progression and morbidity [5]. There is now a large body of data that show systemic inflammation exists in stable COPD and that the intensity of the inflammatory process relates to the severity of the underlying disease [6]. Systemic inflammation has been linked with the extra-pulmonary manifestations in COPD including sudden deaths, arrhythmias, strokes, myocardial infarction, and cancer independent of confounding factors such as age and smoking [4,6,7]. Additionally, in COPD, systemic inflammation has been associated with diminished peripheral muscle strength, reduced exercise endurance, workload, and six-minute walk distance, poor health status, and quality of life [8]. These data suggest that systemic inflammation may be intrinsically involved in the downward spiral in the health status of COPD patients. These data also raise the possibility that treatments modulating systemic inflammation could improve important health outcomes in COPD.

Inhaled corticosteroids are powerful but non-specific anti-inflammatory agents commonly used to treat patients with COPD [9]. Recent studies indicate that although inhaled corticosteroids do not alter the rate of decline in lung function, they reduce bronchial hyperreactivity, decrease the frequency of exacerbations, and slow the rate of decline in the patient's health status [10,11]. A pooled analysis of clinical trial data indicates they reduce mortality by ~25% relative to placebo over three to four years of follow-up [12]. Interestingly, most of the beneficial signal associated with inhaled corticosteroids was observed in a subgroup of COPD patients with moderate to severe disease [12]. In patients with mild disease, there was no survival advantage. These findings are consistent with data on exacerbations, which also demonstrate significant reductions related to inhaled corticosteroids only in those with moderate to severe disease [13]. Intriguingly, biomarkers of lung and systemic inflammation are increased in COPD patients with moderate to severe disease; patients with mild disease generally do not have increased levels of inflammatory biomarkers [14].

Systemic corticosteroids reduce serum C-reactive protein (CRP) and other circulating inflammatory cytokine levels in COPD [15]. They also down regulate certain inflammatory cells and cytokine levels in the airways of COPD patients [16]. Whether inhaled steroids can reduce circulating CRP levels in stable COPD is less certain. A pilot randomized clinical trial of 41 patients with COPD indicated that withdrawal of inhaled corticosteroids increased serum CRP levels by ~70%; whereas a two week treatment with inhaled fluticasone reduced CRP levels by ~50% [15]. These findings are consistent with a recently published observational study by Pinto-Plata and colleagues, who found that users of inhaled corticosteroids had serum CRP levels that were on average ~40% lower than those among corticosteroid non-users [17].

Recent experimental evidence indicates that long-acting β_2_-adrenoceptor agonists on their own can promote translocation of the glucocorticoid receptor complexes from the cytosol to the nucleus, a process that is critical in effecting the anti-inflammatory effects of corticosteroids [18]. When long-acting β_2_-adrenoceptor agonists are added to corticosteroids, the rate of glucocorticoid receptor translocation may be accelerated [19]. Moreover, Zhu and colleagues showed in a randomized controlled trial of 140 patients with moderate to severe COPD, that 12 weeks of treatment with salmeterol plus fluticasone decreased tissue expression of tumor necrosis factor (TNF)-α and interferon (IFN)-γ in the larger airways. They also found that combination therapy decreased sputum eosinophil (p = 0.03) and subepithelial mast cell counts (p = 0.08) in the bronchial tissues [20,21]. Importantly, these cellular changes were accompanied by a reduction in the rate of exacerbations in the combination therapy arm of the study. These results demonstrate that combination therapy decreases local inflammation in the lung, but whether combination therapy reduces systemic inflammation is still unknown.

### Aims of the study

The primary aim of this randomized, placebo-controlled, double-blind, multi-center clinical trial involving 11 centers in Western Canada is to determine whether inhaled corticosteroids alone or in combination with a long acting β_2_-adrenoceptor agonist reduce systemic inflammation in stable COPD.

### Specific objectives

This study will determine whether: 1) fluticasone alone or in combination with salmeterol lowers CRP levels by at least 30% below that achieved by placebo; and 2) combination therapy is better than fluticasone alone in reducing CRP levels. We will also determine whether: 1) CRP reductions are associated with improved health-related quality of life; 2) CRP reductions are associated with improved forced expiratory volume in one second (FEV_1_), and 3) inhaled fluticasone alone or in combination with salmeterol can also reduce interleukin (IL)-6 and other pro-inflammatory biomarkers in COPD.

## Methods/design

### Overview of the study design

This trial is a double blind study comparing the effects of inhaled fluticasone alone or in combination with salmeterol against placebo on serum CRP levels in COPD. All study participants will first undergo a run-in phase during which they will be treated with fluticasone 500 mcg bid for 4 weeks. This will be followed by a withdrawal phase wherein all participants will be free of any inhaled corticosteroids or theophylline products for 4 weeks. After the withdrawal phase, participants will be randomly assigned to one of three arms: placebo; inhaled fluticasone (500 mcg bid); or inhaled fluticasone/salmeterol combination (500/50 mcg bid). Randomization will be carried out centrally according to a computer-generated sequence stratified according to current smoking status with allocation concealment in a 1 (placebo arm) to 2 (fluticasone arm) to 2 (combination arm) distribution ratio. In this phase, all participants and study personnel will be blinded to the treatment assignment. This phase will last for 4 weeks. For safety reasons, during severe exacerbations (i.e. those requiring hospitalization or emergency visit for COPD), the treating physician can break the "code" and place study participants on medications needed to treat the exacerbation (See Figure 1 for protocol summary)

### Details of the run-in phase (4 weeks)

During this phase, all pulmonary medications with significant anti-inflammatory effects (e.g. inhaled corticosteroids, theophyllines, and leukotriene modifiers) will be discontinued. All participants will be maintained on inhaled fluticasone (500 mcg bid; Flovent Diskus^®^, GlaxoSmithKline Canada, Mississauga, ON). Short-acting β_2_-adrenoceptor agonists (e.g. salbutamol) and/or anticholinergic (ipratropium) will be allowed as rescue medications. Long-acting anticholinergic medication (i.e. tiotropium) will also be permitted, if clinically indicated as judged by the participants' attending physician. Long-acting β_2_-adrenoceptor agonists, however, will be prohibited.

### Details of the withdrawal phase (4 weeks)

During this phase, inhaled fluticasone will be discontinued and participants will not be allowed to take any other inhaled corticosteroids, theophyllines or leukotriene modifiers. Short-acting β_2_-adrenoceptor agonists (e.g. salbutamol) and/or anti-cholinergic (ipratropium) inhalers will be allowed as rescue medications. Long-acting anticholinergic inhaler (i.e. tiotropium) will be permitted as maintenance medication. Long-acting β_2_-adrenoceptor agonists will be prohibited.

### Details of the active treatment phase (4 weeks)

All participants will be randomized to one of 3 arms of the trial: placebo (placebo diskus, GlaxoSmithKline Canada, Mississauga, ON), inhaled fluticasone (500 mcg bid; Flovent Diskus^®^, GlaxoSmithKline Canada, Mississauga, ON) or inhaled fluticasone/salmeterol (500/50 mcg bid; Advair Diskus^® ^GlaxoSmithKline Canada, Mississauga, ON). Short-acting β_2_-adrenoceptor agonists (e.g. salbutamol) and/or anti-cholinergic inhaler (ipratropium) will be allowed as rescue medications. Long-acting anticholinergic medication (i.e. tiotropium) will be allowed as maintenance medication if clinically indicated as judged by the participants' attending physician. Any other long-acting β_2_-adrenoceptor agonists or inhaled corticosteroids will not be allowed. As well, theophyllines or leukotriene modifiers will not be permitted in this phase.

### Exacerbations during the study period (see figure 2)

The participants will be instructed at enrollment to contact the local study coordinator at the earliest opportunity if their usual COPD symptoms (i.e. cough, dyspnea, sputum production, or sputum color change) worsen, or if they develop a fever (of unknown source), or active infections elsewhere (e.g. sinusitis). During exacerbations, study coordinators will see the participants as soon as possible and will codify all exacerbations according to Paggiaro's criteria [22]. A mild episode is one that can be self-managed by the patient at home, requiring only intensification of current therapy; a moderate event is defined as requiring antimicrobial and/or oral corticosteroid therapy; and severe is defined as an event requiring admission to a hospital or an emergency department. Treatment decisions during exacerbations will be rendered by the site (principal) investigators using the Canadian Thoracic Society guidelines in consultation with the participants' primary care provider [23]. Blood samples will be obtained at the time of the exacerbation. If participants do not or can not contact study coordinators during severe exacerbations, the study coordinator will make every attempt to obtain blood samples from the patients at the time of their presentation to the emergency department or hospital. For those who experience an exacerbation requiring systemic corticosteroids and/or antimicrobials, the study patients will be asked to return 2 weeks after they finish their course of exacerbation medications at which point their blood, spirometry, and health status measurements will be collected. Once clinical stability is achieved for a minimal of 2 weeks, the participants will resume study participation in accordance to the schedule published in figure 2.

### Study participants

All participants must have a clinical diagnosis of COPD as defined by the Global Initiative for Chronic Obstructive Lung Disease (GOLD) guidelines [24]. Spirometric criteria will include a FEV_1 _of less than 80% of predicted with an FEV_1 _to forced vital capacity (FVC) ratio of less than 0.70 (post-bronchodilator values). Additional inclusion criteria will be a cigarette smoking history of more than 10 pack-years, clinical stability as defined by the absence of exacerbations for at least 4 weeks, and age ≥ 40 years. Exclusion criteria will be any known disseminated malignancy, known chronic systemic infections or inflammatory conditions (e.g. rheumatoid arthritis, systemic lupus erythematosis, active sarcoidosis), previous solid organ transplantation, myocardial infarction or cerebrovascular accident within the past 3 months prior to study enrolment, females of child-bearing age (i.e. must be amenorrheic for at least 12 months), participation in a drug trial within the past 4 weeks prior to study enrolment, any subject who is unlikely to survive more than 6 months, recent upper respiratory tract infection within the 4 weeks prior to enrolment, unable to follow instructions, patients on chronic oral theophyllines and unable or unwilling to come off theophyllines for the study period, oral corticosteroids, or long-term immunosuppressive agents.

### Laboratory & other measurements

#### Blood collection

During every visit (and in the case of an exacerbation and/or infection according to Figure 2), study personnel will take two 10 ml collection of blood from participants through venipuncture using standard techniques. One sample (~10 mls) will be collected in tubes that do not contain an anti-coagulant and another in a tube that does contain an anti-coagulant. The tubes without the anti-coagulant will be allowed to clot for at least 30 minutes, then centrifuged at ≥ 1500 × *g *for 15 min at room temperature and then divided into aliquots (at least 2 serum samples) using a sterile plastic transfer pipet. The serum aliquots will be placed into supplied microtubes containing an anti-protease. Until used, the tubes containing the anti-protease will be stored in a -20°C freezer. The serum samples mixed with the anti-protease will be temporarily stored in a portable cooler containing frozen gel-packs and refrigerated at 4°C. Same-day shipment of the serum samples will be organized by the participating site to the central core laboratory located James Hogg iCAPTURE Centre for Cardiovascular and Pulmonary Research, St. Paul's Hospital, Vancouver, British Columbia, using a courier service, guaranteeing arrival within 24 hours of shipment. The tube with the anticoagulant will be temporarily stored in a portable cooler containing frozen gel-packs and refrigerated (4°C) until same day shipment to the central coordinating centre's laboratory in Vancouver occurs. From these samples, the participants' serum C-reactive protein (CRP) levels will be determined using a commercially available high-sensitivity enzyme-linked immunosorbent assay (ELISA) kits (Alpha Diagnostics, San Antonion, Tx). Serum concentrations of IL-6, TNF-α, and other inflammatory mediators will also be measured using commercially available ELISA kits.

#### Spirometry

Spirometry will be performed for each participant at each visit in accordance with the guidelines from the American Thoracic Society [25]. A test session will consist of several repeated FVC maneuvers. Each maneuver will require the subject to take the deepest possible breath and exhale into a spirometer as hard, fast, and completely as possible. The spirometer will record the volume of air exhaled as a function of time. Each subject will perform at least three FVC maneuvers. For a maneuver to be acceptable, it needs to be a maximal exhalation free from cough, excessive hesitation, leak, obstructed mouthpiece, variable effort, or early termination. At the first visit, pre and post-bronchodilator measurements will be done. For follow-up visits, only pre-bronchodilator values will be measured.

#### Health status measurements

During each visit, a disease-specific health measure, St. George's Respiratory Questionnaire (SGRQ), will be administered by the study co-ordinator at each site [26]. The scores for each section including symptom score (frequency and severity), activity score (activities that cause or are limited by breathlessness), and impact score (social functioning, psychological disturbances resulting from airways disease), as well as a total score will be calculated using established methods [26].

### Outcomes

#### Primary endpoint

The primary endpoint of the study is serum CRP level. We anticipate that inhaled fluticasone alone or in combination with salmeterol will reduce CRP levels by at least 30% below that achieved by placebo. We will also determine whether combination therapy reduces CRP levels beyond that achieved by fluticasone mono-therapy.

#### Secondary endpoints

The secondary endpoints will include: 1) changes in other inflammatory mediators such as IL-6, TNF-α, and monocyte chemotactic protein (MCP-1); 2) changes in SGRQ scores; 3) changes in FEV_1_; and 4) rates of exacerbations

### Statistics

#### Main analysis

For the primary analysis, we will compare the changes in CRP at 4 weeks from baseline between those assigned to inhaled fluticasone alone or in combination with salmeterol and those assigned to placebo based on an intention-to-treat principle. We will use between group t-tests to determine whether the changes in CRP between the groups are statistically significant and a mixed effects model to adjust for any significant differences in the baseline characteristics of the study participants across the groups.

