#### Sample size calculation

We will enroll 250 participants with COPD for this study. This will permit 100 participants to be assigned to fluticasone and combination treatment groups, respectively, and 50 participants will be exposed to a placebo during the active treatment phase. We have calculated our sample size based on the following assumptions: 1) we anticipate that fluticasone relative to placebo will lower baseline CRP levels by ~1.5 mg/L with standard deviation of 3.5 mg/L; 2) we will perform between group comparison of CRP (from baseline) using independent two sample t-test at alpha of 0.05 (two-tailed) and a power of ≥80%.

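### The primary test is an unadjusted t-test on one CRP change score, and earlier pre-randomisation CRP values that the trial collects have no stated role in it

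*Protocol article*

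**What the plan says.** The protocol article, under Main analysis, sets the primary comparison: "we will compare the changes in CRP at 4 weeks from baseline". The test is a between-group t-test. A second method is named alongside it, "a mixed effects model to adjust for any significant differences in the baseline characteristics of the study participants across the groups". Its response variable, random effects and visits are not given.

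The Sample size calculation rests on the same test, an "independent two sample t-test at alpha of 0.05 (two-tailed) and a power of ≥80" per cent, with fluticasone expected to "lower baseline CRP levels by ~1.5 mg/L with standard deviation of 3.5 mg/L" relative to placebo.

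Under Blood collection, samples are taken "During every visit (and in the case of an exacerbation and/or infection according to Figure 2"), and serum CRP is determined from them. The Overview of the study design puts two phases before randomisation: 4 weeks on fluticasone, then 4 weeks without inhaled corticosteroid. The Spirometry section separates a first visit from follow-up visits.

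**The concern.** A change score carries the full noise of a single baseline reading into the endpoint. Using the baseline as a covariate avoids that. Further pre-randomisation readings, if they correlate with the week-4 value beyond what the last reading explains, reduce the noise again.

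The design appears to supply such readings. A first visit comes before 8 weeks of run-in and withdrawal, and CRP is measured at each visit. Yet Main analysis uses one baseline, and no other CRP value is given a task in the primary comparison. The mixed model does not clearly fill the gap, because adjustment through it is tied to baseline differences that turn out significant. At stake is the width of the confidence interval for each primary contrast.

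**Working it through.** **Inputs from the protocol (Sample size calculation).** "We will enroll 250 participants with COPD for this study"; 100 in each active arm; "50 participants will be exposed to a placebo during the active treatment phase"; difference 1.5 mg/L; SD 3.5 mg/L; two-sided alpha 0.05.

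**Assumptions, not in the protocol.** Within-patient correlation of CRP (rho) from 0.3 to 0.8, equal between all pairs of visits; one, two or three usable pre-randomisation values (k).

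**1. The plan's own power figure.** For 100 fluticasone against 50 placebo:

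- Standard error = 3.5 × sqrt(1/50 + 1/100) = 0.606.
- 1.5 / 0.606 = 2.474, and 2.474 − 1.960 = 0.514.
- Power = 69.6% (normal) or 69.1% (noncentral t).

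The stated 80% or more is not reproduced. That is a separate sample-size matter. It is used here only as the starting point for the power figures in step 4.

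**2. Residual variance, in units of the variance of one CRP value.**

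- Change score: 2(1 − rho).
- Week-4 CRP adjusted for k earlier values: 1 − k·rho² / (1 + (k − 1)·rho).

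At rho = 0.5:

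- change score: 2 × 0.5 = 1.000
- k = 1: 1 − 0.25 = 0.750
- k = 2: 1 − 0.50/1.5 = 0.667
- k = 3: 1 − 0.75/2 = 0.625

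**3. Gain beyond one-baseline adjustment** (ratio to k = 1).

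| rho | k = 2 | k = 3 |
|---|---|---|
| 0.3 | 0.947 | 0.913 |
| 0.5 | 0.889 | 0.833 |
| 0.7 | 0.830 | 0.760 |
| 0.8 | 0.802 | 0.726 |

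The second value removes about 5% to 20% of the variance, and the second and third together about 9% to 27%. At rho = 0.5 this equals a trial 1/0.889 = 1.125 or 1/0.833 = 1.20 times as large.

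**4. How the total gain over the change score splits.** At rho = 0.5 the variance falls from 1.000 to 0.667 with two values, a cut of 33%. Of those 33 points, 25 come from replacing the change score by adjustment for one baseline and 8 from the second value. Power at 50 against 100, taking 3.5 as the SD of the change (69.6% for the planned test at every rho):

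| rho | k = 1 | k = 2 | k = 3 |
|---|---|---|---|
| 0.3 | 86.6% | 88.4% | 89.5% |
| 0.5 | 81.5% | 85.8% | 87.9% |
| 0.7 | 76.5% | 83.8% | 86.8% |
| 0.8 | 74.2% | 82.9% | 86.4% |

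The protocol does not say whether 3.5 is the SD of a change or of a level. If it is the SD of a single level, power at rho 0.3, 0.5 and 0.7 is 55%, 70% and 89% for the change score, and 76%, 86% and 97% with two values.

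**5. A less favourable correlation.** Under a first-order autoregressive structure with correlation rho between successive visits, week 4 and the visit before the randomisation visit correlate at rho². Given the randomisation value, the remaining covariance is rho² − rho × rho = 0. The earlier value then adds nothing, whatever rho is.

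**The case against.** The strongest reply is that nothing here is an error. A randomised comparison of change scores is unbiased and matches the test used for sizing, and most of the available gain needs only one baseline covariate. The extra gain rests on equal correlation across values taken in different treatment states (before run-in, on fluticasone, off inhaled corticosteroid) and at least 4 weeks apart. The protocol gives no correlation. All of this stands, and it limits the point to efficiency with an extra gain that may be as low as zero.

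It might also be said that model details belong in an analysis plan that is not shown. That covers the mixed model's silence on its response. It does not cover the primary test, which the article fixes in two places.

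A reader might infer more than the text supports:

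- *That the mixed model is given one change per patient.* Its response is not stated, and a mixed model could take repeated values. Only its stated role can be criticised.
- *That a known number of CRP values is discarded.* Baseline is not defined in Main analysis and the visit figures are not shown. The phases and the first-visit wording imply at least one earlier value; more is likely but unconfirmed.
- *That a repeated-measures model would usefully retain patients without a week-4 sample.* The text describes no visit between randomisation and week 4. Such patients would bring only pre-randomisation values, which say almost nothing about the week-4 contrast.
- *That the change is free.* It uses degrees of freedom and needs a rule for missing covariates.

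**Conclusion.** The point holds as a worthwhile improvement to a method that the article states. The primary test is an unadjusted t-test on one change score, while at least one earlier pre-randomisation CRP value is implied and has no stated role in it. Beyond one-baseline adjustment, the gain in residual variance is about 5% to 20% with a second value and 9% to 27% with a second and third, if the correlation is equal across visits and between 0.3 and 0.8. It is zero under a first-order autoregressive correlation. Leaving the change score for one-baseline adjustment is worth a further 10% to 35% over the same range of rho and is the larger part of the benefit when rho is 0.5 or less. At rho of 0.7 to 0.8, one baseline alone leaves power at 74% to 77% on the protocol's inputs, and a second value brings it to 83% to 84%.

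**What to change.** Define baseline as the end-of-withdrawal (randomisation) CRP. Make the primary analysis a model of week-4 CRP with treatment arm, the baseline CRP as a covariate whether or not the arms differ on it, and the earlier scheduled pre-randomisation CRP values as further covariates. Enter each earlier value separately; do not average them, because they come from different treatment states. Leave unscheduled exacerbation samples out of the covariate set.

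An alternative is a repeated-measures model of all scheduled CRP visits, with visit-specific means common to the arms before randomisation, an unstructured covariance, and the week-4 arm contrasts as the primary estimates. The two are not identical, since they handle missing values differently, so one should be named as primary.

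The cost is one or two degrees of freedom in a trial of 250, a rule fixed in advance for missing covariate values (for example, imputation that uses neither arm nor outcome), and a change of wording. No patients, visits or samples are added.

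### The primary CRP analysis adjusts only for baseline variables that happen to differ significantly, and so forgoes a prespecified adjustment for baseline CRP and the smoking stratum

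*Protocol article*

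**What the plan says.** All places are in the protocol article.

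- **Main analysis, outcome:** "we will compare the changes in CRP at 4 weeks from baseline between those assigned to inhaled fluticasone alone or in combination". The comparator is placebo. Baseline CRP therefore enters by subtraction.
- **Main analysis, test:** "We will use between group t-tests to determine whether the changes in CRP between the groups are statistically significant".
- **Main analysis, adjustment:** the same sentence adds "a mixed effects model to adjust for any significant differences in the baseline characteristics of the study participants across the groups". No covariate is named, and the sentence does not say how this result ranks beside the t-test.
- **Overview of the study design:** the allocation uses a "computer-generated sequence stratified according to current smoking status with allocation concealment". The ratio is 1:2:2 for placebo, fluticasone and the combination. Smoking status does not appear in the Main analysis, Secondary analyses or Sample size calculation sections.
- **Sample size calculation:** "we will perform between group comparison of CRP (from baseline) using independent two sample t-test", with 100 patients in each active arm, 50 on placebo, a difference of about 1.5 mg/L, an SD of 3.5 mg/L, two-sided alpha 0.05 and power of at least 80%. The section does not say whether 3.5 is the SD of the change or of the level.

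**The concern.** Allocation is random and concealed, so a significant baseline difference is a chance event. It shows that the arms differ on that variable, not that the variable predicts CRP. A useful covariate should be prognostic, and baseline CRP and the stratification factor are the obvious candidates before any data are seen. Under the stated rule each is used only if it happens to be imbalanced, while a variable unrelated to CRP is used if it is. The adjusted model cannot be written down in advance.

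Precision is at stake. A simple change score forces the slope on baseline to be 1, whereas ANCOVA estimates it. Leaving out the stratum makes the standard error too large if smoking relates to CRP change. The placebo arm has only 50 patients, so the loss falls on the comparison least able to bear it. A lesser matter is that a reader of the results would not know which figure governs if the t-test and the adjusted model disagree.

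**Working it through.** **Inputs from the article:** difference 1.5 mg/L, SD 3.5 mg/L, two-sided alpha 0.05, 100 versus 50.

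**Assumed, because not stated:** the correlation r between baseline and week-4 CRP; 3.5 as the SD of change; equal variances at the two times.

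**1. The plan's own figure.** SE = 3.5 × √(1/50 + 1/100) = 0.606. Then 1.5/0.606 = 2.474, and 2.474 − 1.960 = 0.514, so power is 69.7% (69.1% by the noncentral t). Pooling the active arms, 200 versus 50, gives 77.4% (77.0%). Neither reaches the stated 80%. That shortfall is a separate matter, but it is the starting point here.

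**2. Change score against ANCOVA.** Let s0 and s1 be the baseline and week-4 SDs.

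- Change-score variance: s0² + s1² − 2·r·s0·s1
- ANCOVA residual variance: s1²(1 − r²)
- Difference between them: (s0 − r·s1)²

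The difference is never negative. It is zero when the slope r·s1/s0 equals 1. For example, with r = 0.8 and s1 = 1.25·s0, both variances are 0.5625·s0². With s0 = s1 the ratio of ANCOVA to change-score variance is (1 − r²)/(2(1 − r)) = (1 + r)/2.

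**3. Power under the assumptions above** (normal approximation; residual SD = 3.5 × √((1 + r)/2)):

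| r | variance ratio | residual SD | 50 vs 100 | 50 vs 200 (pooled) |
|---|---|---|---|---|
| t-test on change | 1 | 3.500 | 69.7% | 77.4% |
| 0.3 | 0.65 | 2.822 | 86.6% | 92.0% |
| 0.5 | 0.75 | 3.031 | 81.5% | 87.9% |
| 0.7 | 0.85 | 3.227 | 76.5% | 83.6% |
| 0.9 | 0.95 | 3.411 | 71.9% | 79.4% |

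The noncentral t gives 81.0% at r = 0.5 and 76.0% at r = 0.7. For 50 versus 100, 80% power needs a residual SD of at most 1.5/(2.802 × 0.1732) = 3.091. The variance ratio is then (3.091/3.5)² = 0.78, so r must be below about 0.56.

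**4. If 3.5 is the SD of the level instead.** For 50 versus 100, t-test against ANCOVA gives 55.2% and 73.7% at r = 0.3, 69.7% and 81.5% at 0.5, and 89.1% and 93.4% at 0.7.

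**5. What the significance rule recovers.** This was simulated with normal data, 50 versus 100, 10,000 runs per setting, and baseline CRP as the only candidate covariate:

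| r | t-test | adjust only if significant | prespecified ANCOVA |
|---|---|---|---|
| 0.3 | 69.0% | 70.5% | 86.3% |
| 0.5 | 69.0% | 69.8% | 80.9% |
| 0.7 | 69.0% | 69.5% | 75.7% |

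Baseline CRP passes the test in only about 5% of trials, so the rule leaves nearly all the precision unused. Under no treatment effect its type I error was 4.2% to 4.9%.

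**6. How often something irrelevant could enter.** With k independent characteristics tested at 0.05, the chance of at least one significant difference is 1 − 0.95^k. This is 23% for 5, 40% for 10 and 64% for 20. The article does not give k.

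**7. Smoking stratum.** The gain depends on how strongly smoking predicts CRP change. The article gives no figure, so none is computed.

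**The case against.** The plan can be defended on several counts, and much of the defence stands.

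- **The t-test on change is valid under randomisation, and baseline CRP is not ignored.** True. The loss is of precision, not validity.
- **The test of significance is fixed.** True. The text gives that role to the t-test, and the sample size rests on it alone. A reader might infer that the data choose the primary test, or that there are two primary answers. The text supports neither. It places an adjusted model beside the t-test without stating its rank.
- **No inflation of type I error.** A reader might infer that the significance rule inflates false positives. The simulation shows it does not. Error of 7.0% to 8.2% appears only if whichever of the t-test and ANCOVA is significant gets reported, and the article does not propose that.
- **ANCOVA is not always more precise.** True: the two are equal when the slope on baseline is 1, even with r below 1. Variances may well differ between the end of withdrawal and week 4, when some patients have restarted treatment.
- **A condensed article leaves model terms to the full protocol or analysis plan.** This holds for a bare list of covariates. It does not cover the rule itself, which is stated and would be carried into any plan that follows the article.

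**Conclusion.** The point holds as one of efficiency and prespecification. The article states a covariate rule based on significance at baseline, which has no sound basis in a randomised trial. A fixed adjustment using data already collected would do better.

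The gain depends on r. With equal variances and 3.5 mg/L as the SD of change, power for 100 versus 50 rises from about 69–70% to between about 72% (r = 0.9) and 87% (r = 0.3). A reader might infer that ANCOVA restores the stated 80%. On these assumptions it does so only if r is below about 0.56, and the article does not give r. The figures apply to CRP in mg/L and not to a log-scale analysis. The cost of omitting the smoking stratum is real only if smoking relates to CRP change, and its size is unknown.

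**What to change.** In the Main analysis section, make the primary analysis one prespecified ANCOVA of week-4 CRP on treatment, CRP at the end of the withdrawal phase and current smoking status. Fit it whatever imbalance is observed. Delete the rule on significant differences, and keep the unadjusted t-test as a supportive analysis. Align the Sample size calculation so that it names the same model, says which SD the 3.5 mg/L is, and states the correlation assumed.

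The cost is a change of wording and a revised power statement. No new data are needed, since blood is taken at every visit and smoking status must be known to randomise. On the raw scale the effect remains a difference in mg/L.

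Log-transforming CRP is a separate decision. It would change the effect measure to a ratio and need its own sample-size inputs.
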